## Abstract

**Background:**

Since 2010, suicide has been the most important cause of mortality in youth aged 15 to 29 years in the Netherlands. Depression is an important risk factor for suicidal behaviors (i.e., suicide ideation, deliberate self-harm, planning, and suicide attempts) in adolescents. Adolescents who develop depressive symptoms, are also at risk for adult depression. This developmental continuity is especially noticeable in adolescents compared to other age groups; therefore, it is necessary to develop preventive strategies for teens. This study will test a multimodal school-based approach to suicide and depression prevention, which integrates universal and targeted approaches and includes various stakeholders (schools, adolescents, parents, and mental health professionals) simultaneously.

**Methods:**

We will perform a cluster randomized controlled trial (RCT) with an intervention and control condition to test the effectiveness of a school-based multimodal stepped-prevention program for depression and suicidal behaviors in adolescents. Adolescents in their second year of secondary education will participate in the study. The participants in the intervention condition will receive the entire multimodal stepped-preventive program comprising early screening and detection of suicidal behaviors and depressive symptoms, a safety net consisting of gatekeepers at school, followed by universal and indicated prevention. The participants in the control condition will undergo only the screening and the safety net of gatekeepers at schools. They will complete assessments at baseline, post-intervention, and 6, 12, and 24-month follow-up. Primary outcome will be suicidal behaviors measured at 12-months follow-up. Additionally, the present study will identify mechanisms that mediate and moderate the program effects and test the effect of the program on various secondary outcomes.

**Discussion:**

If the school-based multimodal stepped-prevention program proves to be effective, it could be implemented in schools on a large scale.

**Trial registration:**

The study is registered in the Dutch Trial Register (NTR6622).

## Background

Each year, 11.2% of Dutch youth have suicidal thoughts and 6.6% attempt suicide or engage in deliberate self-harm [1]. Adolescence is a key period with respect to clinical depression, as the incidence rates of depression rise dramatically from the early to late adolescent years [2]. It is therefore crucial that health care policies focus on preventive interventions that aim to reduce the incidence of depression and suicidal behaviors in early adolescence. We will test a multimodal stepped-prevention program for 12–15 years old and, if effective, implement it in secondary schools in the Netherlands. The program consists of four modules: early screening and detection, gatekeepers training, program targeting stigma, and indicated depression prevention. The current study will examine the overall effectiveness of the multimodal stepped-prevention program for suicidal behaviors and depressive symptoms using a cluster-randomized trial. Through intensive structural collaboration between municipality health services, schools, mental health agencies, and national institutes, we will facilitate an outstanding situation for the implementation of the multimodal stepped-prevention program.

The problem we address is both widespread and severe. In the Dutch population of 17 million, approximately five people per day die from suicide [3]. This affects not only family and friends, but also society. Two studies (in Ireland and Scotland) were conducted to estimate the burden of suicide on society, revealing the cost of €1.5 million per suicide [4, 5]. Suicide before the age of 15 is quite rare, but suicide rates rise substantially during adolescence [2]. To illustrate, suicide is the single most important cause of death among 15 to 29 years old in the Netherlands [3]. It is important to note that suicidal behaviors (i.e., suicidal ideation, deliberate self-harm, and suicide attempts) are often initiated at the age of 15 years; thus, well before a completed suicide [6]. Adolescents themselves recounted that the onset of their suicidal behaviors was when they were 12–16 years old, indicating the need for initiating prevention during early adolescence rather than late adolescence [7]. Therefore, suicidality should in most cases be viewed as a process wherein initial suicidal behaviors remain unnoticed until death by suicide [8, 9]. Suicidal behaviors in young adolescents are sometimes mistaken for behaviors that early adolescents might outgrow [10]. However, approximately one third of adolescents with suicidal ideation will eventually attempt suicide, generally within one year [11]. Moreover, suicidal ideation in adolescence is strongly related to suicidal behaviors in adulthood and is predictive of a range of other adverse outcomes [12–14]. To illustrate, a longitudinal study found that adolescents with suicidal ideation showed significantly more psychopathology and recurrence of suicide attempts and lower perceived coping skills, self-esteem, and social connectedness [15]. Moreover, it appears that suicidal behaviors in adolescents have a high likelihood of recurrence [16]. Adolescents who attempt suicide are more likely to re-attempt suicide compared to adults who attempt suicide [17]. Thus, it is important to recognize adolescent suicidal behaviors at an early stage, take them seriously, and implement strategies to prevent the rise in suicides during adolescence. Studies among adults have indicated that preventive strategies aimed at suicide can indeed reduce suicidal behaviors [18]. Fewer studies have been carried out in adolescents or young adults. Therefore, the aim of this study will be to investigate the effectiveness of a multimodal stepped-prevention program for suicidal behaviors among adolescents, with the aim to implement the program once proven effective.

The existing research has shown that the most common motive for suicide among adolescents is suffering from mental problems [19]. Most adult disorders have their origin in adolescence, with more than three-quarter of disorders starting before the age of 24 [20]. In this context, depression appears to be a significant risk factor for suicidal behaviors in adolescents [21]. This close relationship between depressive symptoms and suicidal behaviors is further established by the fact that the rise of suicidal behaviors in adolescence coincides with increasing incidence of major depression [22]. After all, the first onset of suicidal ideation usually occurs during an episode of depressive disorder in adolescence [21]. In light of this, research suggests that treating depression will likely reduce suicidal behavior as well [23]. Thus, it is important to identify adolescents with subclinical depressive symptoms. Depression is also associated with several negative outcomes. Adolescents with depressive symptoms are more likely to smoke, binge eat [24, 25], and have school-related problems, such as low grades and high drop-out [26, 27]. Once adolescents develop depressive symptoms, they are also at risk for depressive recurrences during adulthood [28]. When a depressive episode initiates during a younger age, the prognosis is far worse than when the first depressive episode initiates during adulthood [29]. This is especially disconcerting considering that depression rates among adolescents have been rising in the past years [30].

In sum, integration of suicide and depression prevention is both a necessary and valuable approach for adolescents. The most relevant setting to reach adolescents is the school, as school attendance is mandatory in the Netherlands until the age of 18. Few school-based prevention programs actually address suicide prevention. Yet, there are some school-based programs aimed at depression prevention have been proven effective in Dutch samples [31, 32]. Current approaches to depression and suicide prevention at schools comprise mostly singular interventions. Growing evidence suggests that depression and suicide prevention warrant the adoption of a multimodal approach to become truly effective [33]. The lack of an integrated multimodal approach is also evident from the available intervention options in the National Institute for Public Health and the Environment (in Dutch: Rijksinstituut voor Volksgezondheid en Milieu, RIVM) and Centre for Healthy Living (in Dutch: Centrum Gezond Leven, CGL) database as well as the healthy school database in the Netherlands [34–36]. Although several programs focus on the recognition of risk factors for suicide or for the prevention of depression, none of these options offer a comprehensive multimodal approach targeting both depression and suicide prevention. Integrating different complementary types of prevention (i.e., universal and indicated approaches) that would include various stakeholders simultaneously (e.g., teachers, adolescents, parents, youth (mental) health service providers) and using various types of interventions (screening, education, universal, and indicated interventions) have been suggested as prevention strategies.

The current study will examine the effectiveness of the multimodal stepped-prevention program for suicidal behaviors and depressive symptoms using a cluster randomized trial. This includes a combination of preventive interventions, such as (1) early screening and detection of suicidal behaviors with subsequent clinical referral, (2) a safety net consisting of gatekeepers at school, (3) universal prevention focusing on stigma reduction, and (4) identification of adolescents who have elevated signs of depression with subsequent indicated prevention. Early detection is important, as less than half of adolescents engaging in suicidal behaviors are known at mental health care services or by other gatekeepers (i.e., family, friends, teachers and mentors at school, etc.) prior to a suicide [37, 38]. A growing body of evidence suggests that school-based screening adequately identifies students at high-risk, effectively refers these students to mental health care, and reduces the risk of suicide ideation and non-fatal suicidal behaviors [39, 40]. It is similarly important that a safety net is created at schools. Mentors should have the knowledge and skills to identify adolescents who show signs of suicidal behaviors and know how to respond to those students [41]. Previous research has shown that a gatekeeper training based on Question, Persuade, and Refer (QPR) model can increase knowledge of suicide prevention and skills [42, 43]. Another important factor impeding identification of suicidal behaviors is the fact that help-seeking behaviors among youths is very low [44]. Nevertheless, research has shown that help-seeking behaviors predicts better prognosis [45]. Stigma has been identified as an important factor that impedes help-seeking among youth. Thus, it is important to develop a universal strategy aimed at reducing stigma.

Stigma literature suggests that mental health literacy combined with information related to individuals’ personal experience is more likely to produce a change in attitude and stigma [46]. Moreover, contact with someone who has personal experience with depression seems to be a crucial factor for changing stigmatizing attitudes [47]. This true not only for students not showing signs of depression or suicidal behaviors, but also for those with mental health problems (e.g., suicidal behaviors or depressive symptoms) when they identify with others suffering from mental health problems [48].

The identification of and subsequent intervention for those with elevated signs of depressive symptomatology should also be important components of the prevention of suicidal behaviors [21]. Cognitive behavioral therapy (CBT) is an effective treatment for depression, and many indicated prevention programs are based on CBT, such as ‘Op Volle Kracht (On Full Power: OVK). OVK was modeled after the Penn Resiliency Program (PRP) [49]. The program successfully reduced depressive symptoms in adolescent girls with subclinical depressive symptoms [50]. A modified OVK version (OVK2.0) by de Jonge-Heesen, et al. [51] will be implemented and investigated at schools with adolescents who have been identified as scoring higher on depressive symptoms, as measured by self-report.

The primary aim of our study will be to investigate the effectiveness of a multimodal stepped-prevention program to reduce suicidal behaviors and depressive symptoms. We hypothesize that suicidal behaviors will decline as a result of a multimodal preventive intervention relative to care as usual enhanced with screening and the gatekeepers’ safety net. Since most modules of the stepped-prevention program are based on depression prevention program, we expect that depressive symptoms will decline as well. Secondary aims are to investigate the mechanisms of change by studying the effect mediators and moderators. Previous research has identified several factors that contribute to lower treatment response in depression and suicidal behaviors. Socio-demographic factors, such as age, gender, cultural background/ethnicity, and educational background, have been found to moderate treatment outcome. Therefore, their effects will be examined. Other factors that could influence treatment outcome are perfectionism, hopelessness, and baseline depressive symptoms and suicidal behaviors. Furthermore, other factors that are related to the proposed prevention modules could mediate outcome, such as stigma, social connectedness, mastery, worry, and life events. We hypothesize that the factors that impede treatment response will have a similar effect on the outcomes of the multimodal stepped prevention program.

## Methods

The study methods and results will be reported in accordance with the CONSORT 2010 statement for reporting parallel group randomized trials [52] and the CONSORT 2010 statement: extension to cluster randomized trials [53]. The medical research ethics committee CMO Region Arnhem-Nijmegen in The Netherlands approved this study (NL61599.091.17). The study is registered in the Dutch Trial Register (NTR6622).

### Design

The presented study is designed as a non-blinded cluster-randomized controlled trial with two parallel groups (experimental and control) to evaluate the effectiveness of a multimodal stepped-prevention program relative to (enhanced) usual care. The participants in the experimental condition will receive all four modules of the multimodal stepped-prevention program, whereas participants in the control condition will receive modules 1 and 2. Randomization will be conducted at school level (to be more precise: at the level of school location because one school can have annexes at multiple locations) to avoid contamination. An independent statistician will randomly assign the participating school locations to the intervention or control condition using random.org. Furthermore, randomization will be stratified for (1) education level (vocational training as one category, in Dutch: VMBO; and higher education / pre-university as the other category, in Dutch: HAVO/VWO) because school type is a relevant prognostic predictor of outcome [54]. Like most psychological and public health interventions, blinding of participants is not possible; therefore, it will not be attempted. The assessments will be conducted at baseline (T0), during the intervention phase after the third module (T1), at post-intervention (T2), at 6-month follow-up (T3), at 12-month follow-up (T4), and at 24-month follow-up (T5). The overall study design is shown in Fig. 1.

**Fig. 1 Fig1:**
[figure not shown]
Schematic Overview of the Study Design

### Participants’ eligibility

Adolescents in their second year of secondary education will be eligible to participate in the study. Inclusion criteria are aged between 11 and 15 years and sufficient knowledge of the Dutch language. Exclusion criteria are absence of (parental) permission and for the indicated module (OVK2.0) already receiving health care for mood-related problems.

### Recruitment

Following the randomization at the school level, as mentioned above, students in their second year of secondary school (i.e., 8th grade in the US), from vocational training up to pre-university level, will receive written information about the screening and the study. Written informed consent from adolescents and their parents will be obtained prior to the initiation of the study.

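### Students and parents are approached for consent after their school has been randomised in an open cluster trial, with no stated concealment of the allocation until consent is given

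*Protocol article*

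**What the plan says.** Four statements in the protocol article settle the order of events and its consequences.

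- **Order of steps (Recruitment).** "Following the randomization at the school level, as mentioned above, students in their second year of secondary school" "will receive written information about the screening and the study". The same section adds: "Written informed consent from adolescents and their parents will be obtained prior to the initiation of the study".
- **Entry depends on consent (Participants' eligibility).** "Exclusion criteria are absence of (parental) permission", together with a further exclusion that applies only to the indicated module.
- **No blinding (Design).** "The presented study is designed as a non-blinded cluster-randomized controlled trial with two parallel groups". Of participants it says: "blinding of participants is not possible; therefore, it will not be attempted".
- **The arms differ visibly (Design).** "Randomization will be conducted at school level", more exactly by school location. Intervention schools receive all four modules, "whereas participants in the control condition will receive modules 1 and 2".

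The related provisions are an intention-to-treat linear mixed model with baseline VOZZ as covariate (Analysis), and entry of demographic variables, VOZZ or CDI-2 as covariates if they differ between conditions at baseline (Other study parameters). The article also commits to reporting under the cluster extension of CONSORT (opening of Methods).

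**The concern.** In a cluster trial, randomising schools makes the schools comparable in expectation. It makes the enrolled students comparable only if the decision to enrol cannot respond to the allocation. Here that decision is taken after the draw. If staff or families know that a school will run the stigma game and the depression course, families of at-risk students may be drawn in or put off, and the two arms may enrol different kinds of students. The direction cannot be predicted. The article itself names stigma as a barrier to help-seeking (Background), so refusal related to risk is plausible.

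An intention-to-treat analysis keeps students in the arm of their school, but it starts from those who entered. A difference created at entry is a bias, so a larger sample does not shrink it. The number of schools implied by the sample size is small, so an unusual consent pattern in one school could move a whole arm.

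**Working it through.** **1. Does consent really follow randomisation?** Recruitment places the written information after the school-level draw. Informed consent cannot come before the information, so it also follows the draw. The statement that consent precedes the start of the study fixes consent relative to study start, not relative to randomisation. The two sentences agree with each other and leave entry as a post-randomisation event.

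**2. How many schools?** The article gives no figure on recruitment to reproduce. Its sample size serves only to gauge the number of clusters.

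- Inputs (Sample size): 215 students per school, 645 per arm, 1290 in total, 30% dropout.
- 645 / 215 = 3 schools per arm.
- 1290 / 0.70 = 1842.9, or 1843 rounded up, against 1844 stated. The difference is immaterial.
- 1844 / 215 = 8.6 schools in total, if every student in a school took part.

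**3. How large could the effect be?** The article gives no consent rates, so all selection inputs below are assumed.

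*Illustration A.* Consent is 80% in control and 70% in intervention schools. The extra refusers lie 0.3 to 0.5 SD above the mean of control consenters on VOZZ.

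- Shift before adjustment = (p_control − p_intervention) × excess / p_intervention.
- Low: 0.10 × 0.3 / 0.70 = 0.043 SD. High: 0.10 × 0.5 / 0.70 = 0.071 SD.
- With these signs the intervention mean is lowered, which flatters the program. Reversed consent rates would do the opposite.

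*After the planned baseline adjustment.* Suppose selection acts only through the true VOZZ level and that level carries forward one for one. Adjustment then leaves about (1 − reliability) × shift. The article gives 0.91 (Cronbach's alpha) and 0.82 (an r of unstated type) under Primary outcome measure. Taking these as reliabilities:

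- Smallest: (1 − 0.91) × 0.043 = 0.004 SD, and 0.004 / 0.38 = 1% of the target d.
- Largest: (1 − 0.82) × 0.071 = 0.013 SD, and 0.013 / 0.38 = 3% of the target d.

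*Illustration B.* Ten per cent of students are high-risk and score 1.5 SD higher. All others consent at 70%. High-risk students consent at 70% in one arm and at 60% or 50% in the other.

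- High-risk share of consenters at 70%: 0.07 / (0.07 + 0.63) = 0.100. At 60%: 0.06 / (0.06 + 0.63) = 0.087. At 50%: 0.05 / (0.05 + 0.63) = 0.074.
- Shift before adjustment: (0.100 − 0.087) × 1.5 = 0.02 SD, or (0.100 − 0.074) × 1.5 = 0.04 SD. With equal consent it is 0.
- After adjustment, on the same reasoning: 0.09 × 0.02 = 0.002 SD up to 0.18 × 0.04 = 0.007 SD.

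*Where adjustment does not help.* If the extra refusers differ in something that predicts later VOZZ but is unrelated to the measured baseline variables, such as motivation or parental support, adjustment removes none of that part. In the limit the full shift of illustration A or B would remain. Nothing in the article indicates how far this applies.

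**The case against.** The strongest reply is that only the order of steps is documented, not that anyone knows the allocation when consent is sought. A reader might infer from the open design that families are told their arm before they decide. The article does not say so. Its blinding statement concerns participants in a psychological or public health program, and it does not say when the allocation is disclosed. An identical letter with the allocation withheld would be compatible with the Recruitment section and may stand in the full protocol, which is not shown. This reply stands, and it makes the concern conditional. It does not remove it, because the stated order leaves an opening that the reverse order would close.

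Second, both arms receive screening, referral and gatekeepers. The arms differ only by a short game with introduction and debriefing, and by a course offered only to screen-positive students. This weakens the motive to consent differently but does not exclude it.

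Third, a reader might infer that nothing can show who was lost, since T0 is completed by consenters. That goes too far. The screening section describes VOZZ and CDI-2 screening of all second-year students within a wider health survey, and Table 1 lists screening separately from T0. Those scores might describe students who did not enter. The article does not say whether screening needs the same consent or whether non-entrants' scores may be used, and the imbalance check it states compares only the two conditions.

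Fourth, the primary model adjusts for baseline VOZZ. This stands for selection through VOZZ, as the working shows, but not for unmeasured differences. The CONSORT commitment concerns reporting and does not change the order of steps.

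**Conclusion.** The point holds in a limited form. The article places information and consent after school randomisation in an open trial where permission decides entry, and it states no concealment until consent. Who enters each arm can therefore depend on the allocation if it is known at that moment. Intention-to-treat and baseline adjustment reduce the consequence but do not remove it.

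The size cannot be derived from the article. Under assumed consent patterns, the residual after baseline adjustment is about 0.002 to 0.013 SD if selection runs through VOZZ alone, and larger if it runs through unmeasured factors. It is tempting to divide the unadjusted shift of 0.043 to 0.071 SD by 0.38 and report a bias of 11% to 19% of the target effect. The documents do not support that: the rates are assumed, and the figure ignores the planned adjustment. Nor do they show that differential recruitment will occur.

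This is a cheap improvement to a stated step, of moderate severity. It is best made before recruitment, because analysis cannot fully repair selection at entry.

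**What to change.** - Recruit the schools and send every family the same letter describing both possible conditions. Close consent, and collect T0 where the timetable allows. Only then should the independent statistician already named under Design draw or release the allocation.
- Where a school needs earlier notice, keep the identical letter and withhold the allocation from students and parents until consent closes.
- If either safeguard is already in place, say so under Recruitment.
- Report the numbers approached and consented per school and arm. If the consent rules permit, compare screening VOZZ and CDI-2 of entrants and non-entrants by arm.

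The cost is less lead time for intervention schools. Modules III and IV need a researcher, mentors, experiential experts or mental health professionals, and two trainers with a three-day training, so staffing and timetabling would be tighter. The fallback of withholding the allocation only from families avoids most of that. Otherwise the change is one of sequence, one common letter and a few extra lines of reporting.
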